# Effects of Internet of Things-based power cycling and neuromuscular training on pain and walking ability in elderly patients with KOA: protocol for a randomized controlled trial

**DOI:** 10.1186/s13063-022-06946-x

**Published:** 2022-12-13

**Keywords:** Knee osteoarthritis, Power cycling, Neuromuscular exercise, Internet of Things, Telerehabilitation

## Abstract

**Background:**

Osteoarthritis (OA) is a common and highly disabling disease that imposes a heavy burden on individuals and society. Although physical therapy is recommended as an important method to relieve OA symptoms, patients cannot continue treatment after returning home. Research on Internet telerehabilitation for knee osteoarthritis (KOA) can reduce pain and improve patient quality of life, and Internet of Things (IoT)-based telerehabilitation is a new form of delivering rehabilitation. This study will evaluate the effect of telerehabilitation via IoT, as a medium to deliver exercises, on pain and walking in patients with KOA.

**Methods:**

This study is a single-blind randomized controlled trial. We will recruit 42 middle-aged and elderly patients with KOA aged ≥ 50 years and randomly divided into power cycling group, neuromuscular exercise group, and control group, and intervention will last for 12 weeks. Outcome measures will be taken at baseline and 4 weeks, 8 weeks, and 12 weeks post-intervention. The pre- and posttreatment differences in knee pain and physical function between participants undergoing power cycling and neuromuscular training and those in the control group will be determined by each scale. The effectiveness will be assessed by the Western Ontario and McMaster Universities Osteoarthritis Index Score (WOMAC) and an 11-point numerical pain rating scale. Walking function and quality of life will be assessed by the timed up and go and walk test, 6-min walk test, and quality of life health status questionnaires.

**Discussion:**

The findings from this trial will establish the feasibility and effectiveness of IoT-based power cycling and neuromuscular training on elderly patients with KOA in the community. As a result, this trial may help provide experimental evidence for finding a better exercise method suitable for elderly patients with KOA in the community.

**Trail registration:**

Chinese Clinical Trials Registry ChiCTR2200058924. Prospectively registered on 6 May 2022.

**Supplementary Information:**

The online version contains supplementary material available at 10.1186/s13063-022-06946-x.

## Background

Osteoarthritis (OA) refers to a chronic degenerative bone and joint disease caused by a variety of factors, and its clinical symptoms include joint pain, deformity, and motor dysfunction [1]. Globally, 9.6% of men and 18.0% of women aged 60 years and older are living with symptomatic osteoarthritis [2, 3]. OA is widely recognized as a major health problem [4], affecting the quality of life of elderly patients and leading to a huge economic burden [5–7]. It has been reported that nearly 250 million individuals suffered from OA worldwide, and the overall prevalence of primary OA in people over 40 years old in China is as high as 46.3% [5, 8]. OA prone to occur in the knee, hip, and hand joints, of which the knee joints are the most commonly affected site according to previous report [5]. Epidemiological survey showed that the incidence of knee osteoarthritis (KOA) is approximately 16–17%, with an increasing trend year by year. In addition, patients aged among 50 to 70 are more likely to be affected [6, 7]. Exercise therapy, as a core option for KOA treatment, has been recommended by various guidelines [9–11]. Exercise with on-site supervision given by physiotherapists has been proven effective for patients with KOA [5]. However, patients who in rural and remote area, from where the population accounts for a large proportion [8], may have difficulties in getting access to in person guidance when exercising; therefore, to establish a way, prescribing exercises should be incorporated for consideration in the development of a treatment plan that bridges physicians and patients. Telerehabilitation has emerged since 1998 [12]. Telerehabilitation refers to providing patients with continuous rehabilitation services through the use of information and communication technology, with combination with telemedicine [13]. The main contents of telerehabilitation include health education, exercise training, self-management, online follow-up, and regular assessment [13, 14]. Previous study demonstrated the feasibility and safety of telerehabilitation in practical applications [15]. Comparing with in-person forms, telerehabilitation showed no statistic difference in the fields of reducing pain and improving patients’ quality of life [14, 16]. With the popularity of the Internet among the elderly population and the development of modern technology, the platform of telerehabilitation has gradually transitioned from telephone to the Internet and the emerging Internet of Things (IoT) [14, 17]. The Internet of Things refers to a network that is extended on the basis of the Internet, and the user terminal can be extended to anything for information exchange, communication, and more intelligent interactive mode, which is a newly developed form of telerehabilitation. Studies have proven that compared with telephone and DVD digital discs, the guidance of the IoT can improve patients’ self-efficacy [18, 19].

A recent review has put forward a city planning concept, highlighting on constructing a healthy and sustainable city [20]. To achieve this goal, it is indispensable to take medical treatment into consideration, especially for those specific types of chronic non-infectious diseases. For patients with KOA, it takes a lot of time for them to go for doctors or physiotherapists in hospitals on-site, which brings heavy medical and social burdens; therefore, KOA treatment will shift to IoT form, which will be an inevitable trend. Our previous research on the Chinese model of IoT-based KOA rehabilitation showed that IoT rehabilitation can ensure that doctors and therapists keep abreast of the patient’s condition and give appropriate treatment, while also strengthening the communication between doctors and patients [21]. Combining IoT with patient exercise to provide community rehabilitation, giving patients living in remote areas the opportunity to communicate with physicians in real-time, supporting ongoing rehabilitation services for patients with KOA [13, 22], has the potential to increase engagement and outcomes for patients with KOA.

Due to the poor physical function of elderly patients with KOA, low-intensity, slow-moving aerobic exercise should be recommended. Power cycling is a low-load and no-impact form of aerobic exercise that help patients with KOA alleviate pain improve range of motion, muscle strength of lower extremities, and cardiorespiratory endurance [23]. In addition, neuromuscular training, as one of another commonly used clinical exercise for KOA patients, has received increasing attention due to its simple and easy-to-learn exercises. Previous studies have demonstrated that regular power cycling and neuromuscular training can both relieve knee pain and stiffness, improve motor function of lower extremity and patients’ aerobic exercise capacity, and lower extremity strength and quality of life for KOA patients [24–30]. In summary, we have learned about the benefits and convenience of power cycling, neuromuscular training, and telerehabilitation in the rehabilitation of patients with KOA. To better deliver the above exercises, we need to further clarify how the combination of the IoT and specific rehabilitation therapy can help patients with KOA in the community. The IoT has been widely used in various fields of social life, and the medical field is also being studied in depth. Several studies have been conducted, including projects such as “Join2Move,” “PainCOACH,” and “Help My Knees,” to explore the feasibility and effectiveness of Internet-based rehabilitation for patients with KOA [31, 32]. However, to our knowledge, no studies have demonstrated whether power cycling and neuromuscular training via IoT can effectively reduce pain and promote improvements in physical function and quality of life in patients with KOA in the community.

## Methods

### Aim

The primary objective of this study is to compare the effect of IoT-based power cycling and neuromuscular training on the elderly patients with KOA in the community. Whether the intervention of elderly patients with KOA is effective or not provides experimental evidence for finding a better exercise delivery mode for elderly patients with KOA in the community.

### Study design

This study is a 12-week single-blind randomized controlled trial. The trial intervention and data collection will be completed from September 2022 to June 2023. The protocol was designed following the Recommendations for Interventional Trials (SPIRIT) and SPIRIT checklist could be found in Additional file 1 [33]. The trial will be conducted in the community in Chengdu, Sichuan Province. Assessments would perform online.

### Participants and setting

We will recruit 42 participants at West China Hospital, Sichuan University, in Southwest China. Ethics approval was obtained from Ethics Committee on Biomedical Research, West China Hospital of Sichuan University, and prospectively registered on the Chinese Clinical Trials Registry (ChiCTR2200058924) registered 6 May 2022.

### Inclusion criteria

Participants are potentially eligible if they (i) have knee pain and could provide with previous diagnosis certificate from a regular medical institution or are diagnosed with KOA according to the Guidelines for Diagnosis and Treatment of Osteoarthritis in China (2021 Edition) (see Table 1) [8]; (ii) have a I–III Kellgren-Lawrence grade [34]; (iii) are able to use their smartphones to send messages and make video calls using WeChat; and (iv) can communicate in Mandarin and understand Chinese characters.

**Table 1 Tab1:** Inclusion and exclusion criteria

Inclusion criteria
1. Has knee pain and is diagnosed with KOA (provide a relevant diagnosis certificate from a regular medical institution)
2. Accord with following (1) and two criteria from (2) or (3) or (4) or (5):
(1) Recurrent knee pain in the last month
(2) Narrowed joint space, subchondral cyst formation and bone sclerosis, or osteophytosis around joint margin on the radiographs in standing or load position in X-ray
(3) Aged 50 years and over
(4) Stiffness ≤ 30 min in the morning
(5) Palpable bone crepitation (fremitus) on movement of joint
3. Kellgren-Lawrence grade I–III of KOA
4. Be able to use smartphones with an Internet connection and send text messages
5. Be able to communicate in Mandarin and understand Chinese characters
**Exclusion criteria**
1. Diagnosed with rheumatoid arthritis, severe osteoporosis, or other pathological conditions of the knee joint
2. Knee replacement or other knee surgery
3. Receive rehabilitation treatment for KOA in hospitals, clinics, or rehabilitation institutions or participate in other projects related to KOA rehabilitation
4. Uncontrolled hypertension and diabetes (such as fasting blood glucose ≥ 16.7 mmol/L) or repeated episodes of hypoglycemia (blood glucose ≤ 3.9 mmol/L) or other diseases that restrict exercise (such as stroke, heart failure, and severe anemia)
5. Patients with a history of mental disorders
6. Being informed by a doctor that there are other circumstances in which it is inappropriate to exercise without supervision
7. Unable to sign informed consent
8. Unable to communicate with others in normal Chinese
9. Cannot use smartphone or WeChat to send messages and have video calls

### Exclusion criteria

Participants who meet any of the following criteria will not be able to participate in this study if they (i) have rheumatoid arthritis, severe osteoporosis, or other pathological conditions at the knee; (ii) are ready for knee arthroplasty or other knee surgery; (iii) receive KOA rehabilitation treatment or participating in other programs related to KOA in hospitals, clinics, or rehabilitation institutions; (iv) undergo uncontrolled hypertension and diabetes (such as fasting blood glucose ≥ 16.7 mmol/L), repeated episodes of hypoglycemia (blood glucose ≤ 3.9 mmol/L), or other diseases that restrict exercise (such as stroke, heart failure), severe anemia, etc.; (v) are with a history of mental disorders; and (vi) are informed that there are other circumstances that are not suitable for exercises without supervision; (vii) are unable to sign an informed consent.

### Randomization and allocation

After the participants completed the baseline measurements, they were divided into power cycling group, neuromuscular training group, and control group according to the random allocation principle using a computer-generated random allocation table at a ratio of 1:1:1. Then, according to the random number, the corresponding test envelope is obtained, which includes the form for recording participants' information, the intervention plan, and the plan for emergent event to ensure that each participant was only aware of their own experimental interventions.

### Blinding

Due to the characteristic of this trial, participants and physiotherapists will not be blinded to group allocation and will be aware of the alternative treatment options. The study hypotheses will be blinded to participants. The researcher conducting the data collection and analysis will be blinded to treatment allocation.

### Participant timeline

Table 2 shows the assessments at each time point following the SPIRIT statement [33]. Figure 1 demonstrates the flow chart of this trial.

**Table 2 Tab2:**
[figure not shown]
Study assessments at specific time points

**Fig. 1 Fig1:**
[figure not shown]
Flow-chart of the study

### Media for intervention prescription

To realize the connection between Internet and things, we built an applet, called Huaxi Rehabilitation Cloud applet, within the WeChat mini programs platform, by which the participants could receive the prescription of the corresponding interventions. To make it more convenient for usage, we invited public and therapists to involve in the design process of this applet and asked for any suggestions during using the applet in daily routine. After several internal discussions, we optimized the final version (Additional file 2) of the applet and applied in our trial.

### Power cycling group

Participants in this group will conduct three 30-min cycling sessions per week and twelve weeks in total. Participants will perform exercise with power cycling which are set in community before our study launched. Each time participant warms up before exercises and cool down for 5 min after that. The exercise intensity, measured by the rating of perceived exertion (RPE), scores 12–14 points during cycling, that is, with self-efficacy of feeling a little hard [35]. A physiotherapist will supervise participants through a video call weekly, and new exercise prescription will be delivered when participants feel easy or too hard to perform cycling at the pre-set intensity. Doctors and physiotherapists will conduct telerehabilitation assessments, after which they will send exercise prescriptions through applet according to the assessment results. Then, participants scan the QR code typed on the power cycling through the applet to start exercise. If participants have any discomfort during exercise, they can click “End Early” on mobile phone to stop, and the physiotherapist will automatically receive a feedback, and they will decide whether it is necessary to make a new assessment. Besides, the weekly video call session and progressive exercise prescribed by physiotherapist could be considered as a method to monitor potential dropout issue and prevent the loss of follow-up and reduce the number of subjects who violate the allocation plan.

### Neuromuscular training group

Participants allocated in this group will conduct exercises at home three times per week [36]. Details of neuromuscular training exercises could be found in Table 3 [28]. Generally, it comprises weight-bearing training and up-down stepping exercises. After assessments, doctors and physiotherapists will send training videos to participants and have a video call to ensure the exercises are performed correctly. Family members will accompany the participants during each exercise session (including video call with physiotherapists) to ensure safety and to provide any support. Physiotherapists will prescribe planned exercises according to the feedback received from participants weekly. If pain worsen and could not relieve within 24 h after conducting exercises advanced, participants will be asked to continue the former exercises.

**Table 3 Tab3:** Details of neuromuscular training exercises

	**Exercise dose:** 10 sets/session, 3 sessions/time (with a 30–60-s rest between each session), 3 times/week, 30 min/time, 12 weeks in total	
	**Exercise 1**	**Exercise 2**
Weeks 1–2	**Starting position:** standing, feet shoulder-width apart, and the affected side is holding a fixed table **During exercise:** Unaffected lower extremity keeps straight and slides forward and backward on the flat ground, while the affected side, as a support, flexes at the same time. When the unaffected side slides back, the weight-bearing side extends gradually from the flexion position. Participants are required to keep the alignment of the hip, knee, and ankle alignment and place the center of gravity on the affected side	**Step up:** affected side goes up first, with the center of gravity placed on the lower extremity on the affected side. During the flexion-straight process, the affected side is required to perform as slowly as possible, be kept stable, and avoid shake **Step down:** Unaffected side goes down first. Participants complete the action of descending the steps by controlling the affected side to gradually flex from extension. Being slow, being stable, and avoiding shake like up step exercise are also required
Weeks 3–4	On the basis of weeks 1–2, additionally provide a laterally exerted resistance on the affected joint by using elastic band (Thera-Band, yellow). Participants are required to maintain correct alignment of the lower extremity under resistance (hip, knee, and ankle are on the same sagittal plane)	On the basis of weeks 1–2, participants are asked to hold dumbbells of 1 kg in each hand
Weeks 5–6	The same as weeks 3–4, except adding resistance (red elastic band)	The same as weeks 3–4, except adding resistance (2 kg in each hand)
Weeks 7–8	The same as weeks 3–4, except adding resistance (green elastic band)	The same as weeks 3–4, except adding resistance (3 kg in each hand)
Weeks 9–12	The same as weeks 9–12	The same as weeks 9–12

Reference: [28]

### Control group

According to the recommendation by Chinese guideline for diagnosis and treatment of osteoarthritis (2021 edition) and Osteoarthritis Research Society International (OARSI), participants are administrated with glucosamine hydrochloride capsules (pharmaceutical product registration certificate number HC20140008 and produced by Hong Kong Aomei Pharmaceutical Factory), with a dose of 750 mg and 1.5 g/day, to relieve symptoms of KOA [8, 11].

### Common interventions

In addition to the specific and individual interventions for three groups mentioned above, we also set three aspects as common rehabilitation interventions and participants in each group will receive the following information:KOA educationThrough applet, information detailing the knowledge of KOA and clinical guidelines were sent three times per week by doctors and physiotherapists. At the same time, participants can also communicate with healthcare providers through Huaxi Rehabilitation Cloud applet to inquire any health conditions about KOA.Self-managementInformation comprise weight management and emotional management.(a) Weight management: obesity is one of the risk factors of KOA, so here, we emphasize weight control [1]. Participants need to upload their height and weight to the applets every week, and the system will automatically generate a body mass index (BMI). When BMI > 24 kg/m^2^, the doctor will remind the participant to control their weight and send information about weight management and healthy eating. (b) Emotional management: patients with chronic pain and activity limitation are at a high risk of depression [37], and in this study, physical therapists push brochures to participants and communicate and guide them. Ensure adequate sleep (7–8 h a day), chat with friends every day, take a deep breath when troubled, listen to soothing light music when irritable, etc.Exercise education

Participants should do at least 150 min of moderate-intensity (70% of maximum heart rate) aerobic activity per week, such as brisk walking, swimming (freestyle is best), and cycling. Excessive exercise should be avoided, and knee pads and other auxiliary devices should be used to support and protect the diseased joints. You can try team sports under the guidance of a special person, such as group hiking and group gymnastics., in mutual supervision and encouragement, to increase the fun of sports.

### Outcome assessments

Outcomes will be measured at baseline (T0) and at 4 (T1), 8 (T2), and 12 (T3) weeks after the allocation. All participants will be assessed by researchers blinded to group tasks.

### Primary outcome measures

(I) The Western Ontario and McMaster Universities Index (WOMAC) score will be used to assess knee pain, stiffness and physical function. The WOMAC is a self-assessed health status scale for KOA patients consisting of 24 items in three subscales of pain (5 items), stiffness (2 items), and physical function (17 items). All items are scored from 0 (asymptomatic) to 4 (very severe), and the total score ranges from 0 to 96, with higher scores indicating more severe symptoms [38, 39]. The test–retest reliability of the scale was 0.83, and the validity was 0.77 [40]. (ii) The 11-point numerical pain rating scale (11-NRS) was used to assess knee pain 48 h before the test. The 11-NRS is a standard tool for the study of chronic pain. A score of 0 indicates no pain, and 10 indicates severe pain [41].

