### Sample size

The calculation is carried out according to the unified standard of clinical trial reporting and the calculation requirements of the sample size of noninferiority experiments [41, 48]. Based on the previous research results of our research team and comprehensive consideration of previous experience [28], the reduction in pain score in the WOMAC scale was used to assess the improvement of KOA symptoms. The average pain scores in patients with KOA were 1.65, 1.7, and 0 respectively [36, 49]. We set a to 0.05 and test power 1-β to 90%. Calculation via G*Power 3.1 software. A total of 33 participants is required for the calculation. With allowance for a dropout rate of 20%, each group requires 14 enrolled participants.

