### Statistical analysis

Statistical analysis is performed using the SPSS software (25.0). Significance level will be set at 0.05 for all statistical analysis. Intention-to-treat principle will be followed. Baseline comparability between groups of categorical variable data was determined using the chi-square test or other suitable nonparametric tests. Quantitative data will be expressed as the mean (SD), if it follows normal distribution and homogeneity of variance; otherwise, median (IQR) is given. For statistical inference, if the data obeyed a normal distribution and homogeneity of variance and satisfied spherical symmetry, variance analysis of repeated measurements was used; otherwise, the Kruskal–Wallis *H* rank sum test will be conducted. For data that recorded from drop-out participants, maximum likelihood estimation will be used to impute missing data, including any lacks for primary and secondary outcomes. The data collected are kept by people not involved in the trial intervention and by the online platform. The datasets analyzed during the current study and statistical code are available from the corresponding author on reasonable request, as it is the full protocol.

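### Two primary outcomes are each tested at 0.05 with no adjustment, success rule, deciding WOMAC score or deciding visit; separately, the trial is powered on a WOMAC pain score that is not singled out as primary

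*Protocol article*

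**What the plan says.** All references are to the Methods of the protocol article.

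- **Primary outcome measures** lists two instruments. For the first: "The Western Ontario and McMaster Universities Index (WOMAC) score will be used to assess knee pain, stiffness and physical function". It describes three subscales (pain 5 items, stiffness 2, function 17), each item scored 0 to 4, and a total of 0 to 96. It does not say whether the total or a subscale is the primary score. For the second: "The 11-point numerical pain rating scale (11-NRS) was used to assess knee pain 48 h before the test".
- **Outcome assessments** gives the schedule: "Outcomes will be measured at baseline (T0) and at 4 (T1), 8 (T2), and 12 (T3) weeks after the allocation". No visit is marked as the deciding one.
- **Statistical analysis** plans a repeated-measures analysis of variance, with the Kruskal-Wallis test as the fallback. On the error rate it says: "Significance level will be set at 0.05 for all statistical analysis". No adjustment is mentioned, and no rule says whether one or both primaries must succeed.
- **Sample size** uses one quantity: "the reduction in pain score in the WOMAC scale was used to assess the improvement of KOA symptoms". The means are 1.65, 1.7 and 0, alpha is 0.05 and power is 90%. The result is 33 evaluable participants and 14 enrolled per arm after 20% dropout. No standard deviation is given.

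**The concern.** A reader of the article cannot tell which result decides whether the trial succeeded. Either instrument could carry the claim, on the WOMAC total or on a subscale, at any of three post-baseline visits. If a significant result on either primary counts as success, testing both at 0.05 takes the overall false-positive rate above 5%. With 42 participants, leaving the choice open until the data are seen matters.

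There is a second and separate problem. The trial is sized on WOMAC pain alone. If the deciding score turns out to be the WOMAC total or the 11-NRS, the stated 90% power does not apply to it.

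**Working it through.** **Inputs from the article.** Three arms at 1:1:1; 11 evaluable and 14 enrolled per arm; two primary outcomes; 0.05 for every analysis; means 1.65, 1.7 and 0; 20% dropout.

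**Assumed, because not given.** Correlation between the two outcomes 0.5 to 0.8; normal data; no true difference between arms when computing error rates; a back-solved SD for power.

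**Step 1. The plan's own sample size.** The grand mean is (1.65 + 1.7 + 0)/3 = 1.117. The SD of the three means is √[(0.533² + 0.583² + 1.117²)/3] = 0.790. In a one-way ANOVA at alpha 0.05 and 90% power, 33 is the answer only if the within-arm SD is about 1.15 to 1.21 (effect size f = 0.790/SD, about 0.69 to 0.65). The article gives no SD, so 33 can be back-solved but not confirmed. The dropout step does reproduce: 11/0.8 = 13.75, so 14 per arm and 42 in total.

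**Step 2. Error rate for what the text implies: one omnibus test per primary.**

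- If independent: 1 − 0.95² = 9.75%.
- Positive correlation, expected because both instruments measure knee pain, lowers this. Simulated under no effect, it is 8.2-9.3% for week-12 omnibus tests with 14 per arm, and 8.0-8.9% for all-visit group tests with 11 per arm.

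This counts one deciding term per model. The article does not say whether the group term or the group-by-time term decides. If either could, there would be four chances and an independent-test figure of 1 − 0.95⁴ = 18.5%.

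**Step 3. Error rate if arm comparisons at week 12 are added without a gate.** The text does not specify these tests. The figures show what would follow if they were run at 0.05.

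| Tests at week 12, both primaries | Number of tests | Chance of at least one p < 0.05 |
|---|---|---|
| Each exercise arm against control | 2 × 2 = 4 | about 14-16% |
| All three pairwise comparisons | 2 × 3 = 6 | about 18-21% |

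For six independent tests the figure would be 1 − 0.95⁶ = 26%.

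**Step 4. Error rate after the proposed change.** With WOMAC pain at week 12 as the only primary, and pairwise contrasts read only after a significant three-arm test, the simulated rate is 4.8-5.0%. Testing the two exercise-versus-control contrasts at 0.025 each gives 4.4-4.7%. Under no effect, Holm has the same chance of at least one rejection as that split, because its first step is also at 0.025.

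**Step 5. Power if both instruments stay primary at 0.025 each.** This uses the back-solved SD and assumes the same standardised effect on both instruments.

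| SD (assumed) | Power of 33 at 0.05 | Power of 33 at 0.025 | Evaluable for 90% at 0.025 | Enrolled at 20% dropout |
|---|---|---|---|---|
| 1.15 | 93% | 87% | 36 | 45 |
| 1.20 | 91% | 84% | 39 | 51 |

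Enrolment is rounded up per arm: 12/0.8 = 15, and 13/0.8 = 16.25, so 17.

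**The case against.** **The planned analysis is one model per outcome.** Repeated-measures ANOVA takes in all visits and all arms together, and the Kruskal-Wallis fallback is a three-group omnibus test. A reader might multiply instruments, WOMAC scores, visits and arm pairs, and infer a false-positive rate several times 5%. The article does not support that count. The assessment schedule is not a list of tests, and no ungated pairwise test is written anywhere. This part of the objection stands, so the supported figure is about 8-9%. Two things keep the larger figures worth showing as conditional. The Abstract and the Aim promise comparisons with control and between the exercise programmes, which an omnibus test cannot deliver. The fallback also has no visit factor, so it needs a choice of visit that is not stated.

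**The 0.05 statement could be compatible with adjusted p-values, and the detail may sit in an analysis plan that is not shown.** Post-hoc adjustment can be left to such a plan. Still, the article makes a positive statement of 0.05 for everything and names two primaries beside it. Which score and visit decide is part of defining the endpoint. The objection lowers the certainty about what will be done, but it does not remove the gap in what is written.

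**The WOMAC mismatch is ambiguity rather than proven contradiction.** The primary-outcome text says that WOMAC assesses pain among other things, so the pain score may be one of the intended primaries. This stands: the accurate statement is that the powered score is not singled out. It would also be wrong to infer that sizing on the pain score raises the false-positive rate. It bears on power and endpoint definition only.

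**Conclusion.** The point holds in a limited form. Two primaries at 0.05 each, with no adjustment or success rule, give a family-wise error of about 8-9% (9.75% if independent), just under twice the nominal level. This assumes one omnibus test per primary, success on either one, and outcome correlations of 0.5 to 0.8. About 14-16% or 18-21% applies only if ungated week-12 arm comparisons are added, which the text does not specify.

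The second part is independent of the first. The 33 evaluable participants and the 90% power refer to WOMAC pain, and nothing in the article shows that they hold for the WOMAC total or the 11-NRS.

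**What to change.** - **Outcomes.** Name the WOMAC pain score (5 items × 4 points, 0-20) as the single primary outcome, matching the sample size. Move WOMAC total, stiffness and function, the 11-NRS, and weeks 4 and 8 to secondary.
- **Deciding test.** State one test that fits the planned repeated-measures model, for example its between-group contrast at week 12. An all-visit group effect is also possible, provided it is named in advance. State the visit for the Kruskal-Wallis fallback as well.
- **Arm contrasts.** Test pairs at 0.05 only after a significant three-arm test of the same quantity. With exactly three arms this holds the error at about 5% without splitting alpha. Alternatively, apply Holm to the two exercise-versus-control contrasts.
- **If both instruments stay primary.** Split alpha and restate the power for 33 evaluable participants, giving the SD used. At 0.025 each the power would be about 84-87% under the assumptions above, and 90% would need 36-39 evaluable (45-51 enrolled).

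**Cost.** The single-primary route changes wording in the outcome and analysis sections and leaves the sample size as it is. The 11-NRS and WOMAC total lose primary status. If a week-12 contrast is chosen, the overall repeated-measures test no longer decides the trial. Keeping both primaries costs power, or 3 to 9 more enrolled participants (45 − 42 to 51 − 42).
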